## 2. Materials and Methods

### 2.1. Study Design

This was a single-centre, open-labelled, three periods, six sequences, crossover, single-dose oral administration, randomised-controlled trial in healthy volunteers under the fasting condition. Approximately 24 to 27 subjects were screened for a list of inclusion and exclusion criteria (Figure 1) to recruit up to 18 healthy volunteers with the estimation of 30–50% ineligibility. For AP formulation, the time to reach the maximum plasma concentration (Tmax) and the half-life (T_1/2_) were recorded at 1.63 to 2 h and 6 h, respectively [22,23]. In the package insert of metformin, the Tmax and T_1/2_ for metformin are 2 h and 6.2 h [24]. As a result, the wash-out period was determined to be seven days, which is more than five half-lives of the investigation products to ensure that the drug concentrations were below the lower limit of bioanalytical quantification in all subjects at the beginning of the next period [25]. Eligible subjects were randomised in a ratio of 1:1:1 into either metformin 1000 mg, AP capsules 1000 mg, or AP capsules 2000 mg. Figure 2 describes the SPIRIT schedule of enrolment, assessment, and intervention for the explanation to the trial subjects.

In the early-phase clinical trial, absorption, distribution, elimination, and its interaction and adverse reactions were studied in pharmacokinetics [26]. A bioavailability study measures the rate and extent of the active ingredients from the pharmaceutical dosage into the site of action, and provides information for the absorption, distribution, and elimination of a compound through a plasma concentration–time curve [27]. Generally, a crossover design is potentially affected by carry-over effects, sequence assignment, subject drops-out, and difficulties in analyses [28]. The crossover study was chosen in this single-dose oral administration proof-of-concept trial to reduce the number of subject recruitment and reduce the intrasubject variability in the metabolomics analyses. In addition, the relative short half-life of the investigational products also reduced the carry-over effects and shorten the trial period when compared to the parallel design.

The rationale of metformin selection as a model drug includes the well-known safety profiles of the first line antihyperglycemic drug and its inconclusive mechanism of action. There have been several metabolomics analyses for metformin on healthy volunteers and patients, and the perturbed human metabolic pathways associated with the pharmacodynamics effects remain inconsistent [29]. Therefore, this study focussed on the individualised pharmacokinetic guided Cmax samples to investigate the dysregulation of metabolic pathways under a controlled environment. The AP capsule is a traditional medicinal product registered under the Ministry of Health Malaysia for general well-being [30]. Several clinical trials conducted have demonstrated the effects on diabetes, ulcerative colitis, and upper-respiratory tract infections [19,31,32]. Most of the traditional herbal medicine could not provide evidence of the pharmacokinetics of multi-components in the drug development process. Kantae et al. proposed that the discovery of metabolite biomarkers using pharmacometabolomics could predict the pharmacokinetic and pharmacodynamic effects [33]. Therefore, this proof-of concept crossover study was designed to investigate individualised pharmacokinetic and pharmacometabolomic studies on metformin in the first analysis set as a model drug, followed by AP using a similar analysis framework in the second analysis set with additional dose-dependent effects. The dysregulated human metabolic pathways associated with the diabetic effects for the three investigational products were then compared.

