### Objectives

The study aimed to determine the safety of metformin 1000 mg, AP capsules 1000 mg, and AP capsules 2000 mg in the clinical part.

In the pharmacokinetics and metabolomics analyses, metformin 1000 mg will be used as a model drug for the determination of the pharmacokinetic parameters including the Cmax, Tmax, half-life (T1/2), and AUC0-infinity. The individualised Cmax of metformin will be used for the metabolomics analyses to identify dysregulated human metabolic pathways that are associated with diabetic effects.

The AP 1000 mg and AP 2000 mg analyses will follow the pharmacokinetics and metabolomics framework from the metformin arm in the second analysis. The pharmacokinetics for AP 1000 mg and AP 2000 mg will be compared for the three bioactive compounds, andrographolide, neoandrographolide, and deoxyandrographolide. The dysregulated human metabolic pathways identified from the metabolomics analyses for two doses will be compared based on the dose-dependent effects. 

Finally, the dysregulated human metabolic pathways associated with the diabetic effects will be compared for all three intervention arms.

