### 3.3. Untargeted Metabolomics and Multivariate Data Analysis

In the metformin analyses, pharmacometabolomics analysis will be performed to explore the human metabolic pathways between the pre-dose and peak plasma concentration. The samples will be analysed using Agilent LCMS-QTOF for an untargeted metabolomics approach following the literature method with some modification [47]. The samples will be analysed using a reverse phase column with a guard column in both the positive and negative modes. The instrument method setting will follow the METLIN analysis methods [48]. The pool quality control samples will be used to condition the column and visualisation checking for the batch analysis.

The untargeted metabolomics workflow is presented in Supplementary Figure S8. The chromatograms will be converted to the mzXML file using Global Natural Products Social (GNPS) package, University of California San Diego, California, United States [49]. MS spectral processing, normalisation, batch correction, multivariate analysis, and functional metabolic pathway analysis will be run on MetaboAnalyst web-based application (McGill University, Montreal, QC, Canada) to identify the human metabolic pathways [50]. In the multivariate analyses, principal component analysis (PCA) and partial least square discriminant analysis (PLSDA) will be used to inspect the region’s separation among the analysed time points. After this, a t-test will be used to identify the significantly differentiated compounds between the two-time point groups. The significant features will be processed in MS peaks to a pathway module to identify the dysregulated human metabolic pathways according to the Kyoto Encyclopaedia of Genes and Genomes (KEGG) database.

A similar analysis framework for metformin as described above will be repeated for AP 1000 mg and AP 2000 mg. There will be a head-to-head comparison of the pharmacokinetic profiles for both the AP arms. After this, the pharmacometabolomic identified dysregulated human metabolic pathways will be compared for the two doses in AP to investigate the dose-dependent effects. Finally, the dysregulated human metabolic pathways associated with the diabetic effects for the metformin, AP 1000 mg, and AP 2000 mg will be compared.

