### 3.4. Reporting Framework

The study will be designed to use metformin as a model drug in the application of targeted peak plasma concentration in the metabolomics study. The clinical safety data, method validation, pharmacokinetics and metabolomics results of metformin will be reported in detail. This report suggests an application model for individualised pharmacokinetics and pharmacometabolomics study in an early-phase clinical trial in the drug development program. The results and the proposed pharmacometabolomic application framework in an early-phase clinical trial for the first analysis using metformin was recently published [51].

In the second report, the pharmacokinetics profiles for AP 1000 mg and AP 2000 mg will be presented. The results will include the dose-dependent effects of the dysregulated human metabolic pathways associated with the pharmacological effects. This report will suggest another application model for the pharmacokinetics and pharmacometabolomics study using multi-component herbal medicines in an early-phase clinical trial. Additional dose-dependent effects will be described in the report. Finally, the dysregulated human metabolic pathways associated with the diabetic effects will be compared for metformin and AP.

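### Metformin is analysed in a first set and both AP doses in a later one; if these were separate LCMS-QTOF runs, comparing per-arm pathway lists can show drug differences that come from the run

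*Protocol article*

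**What the plan says.** The order of analysis appears in four places in the protocol article.

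- Objectives: "The AP 1000 mg and AP 2000 mg analyses will follow the pharmacokinetics and metabolomics framework from the metformin arm in the second analysis".
- Section 2.1: the study works "on metformin in the first analysis set as a model drug, followed by AP using a similar analysis framework in the second analysis set".
- Section 3.3: after the metformin workflow, from LCMS-QTOF acquisition to pathway mapping, "A similar analysis framework for metformin as described above will be repeated for AP 1000 mg and AP 2000 mg".
- Section 3.4: the framework and results "for the first analysis using metformin was recently published". The AP results are left to a second report.

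Within an arm the contrast is pre-dose against peak: "pharmacometabolomics analysis will be performed to explore the human metabolic pathways between the pre-dose and peak plasma concentration". A t-test picks the features that differ between the two time points, and the significant ones go to pathway mapping. The cross-drug step follows: "Finally, the dysregulated human metabolic pathways associated with the diabetic effects for the metformin, AP 1000 mg, and AP 2000 mg will be compared".

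On run effects, section 3.3 says that "MS spectral processing, normalisation, batch correction, multivariate analysis, and functional metabolic pathway analysis will be run on MetaboAnalyst". It names no correction method. Pooled quality-control samples are given two uses, column conditioning and a visual check. No common quality control, bridging sample or joint run of the three arms is described. Section 2.3.7 mentions processing batches without saying which arms each batch holds.

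**The concern.** Every subject receives all three treatments, and section 2.1 gives lower variability in the metabolomics analyses as a reason for the crossover. That benefit reaches the metformin-versus-AP objective only if the two drugs are measured on a comparable footing.

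Untargeted LCMS-QTOF gives relative intensities. Noise, sensitivity and the set of detected features can differ between runs. If all metformin samples sit in one run and all AP samples in another, a run difference and a drug difference look alike wherever each arm's own pre-dose samples do not remove the run effect.

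The planned comparison is exposed to this because it compares which features and pathways reached significance in each arm, and significance depends on noise and detection as well as on the drug effect. A pathway reported for metformin but not for AP could mean only that the second run was noisier. This comparison is the last stated objective.

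**Working it through.** The plan gives no alpha, power, effect size or SD for the metabolomics, so there is no figure of its own to reproduce. Two checks were made.

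**1. What can be estimated if run 1 holds metformin and run 2 holds both AP doses**

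| Model | Columns | Rank | Metformin vs AP estimable? |
|---|---|---|---|
| Peak samples only: intercept, AP 1000, AP 2000, run | 4 | 3 | No |
| Pre-dose and peak, additive run shift: intercept, run, time, AP 1000 × time, AP 2000 × time | 5 | 5 | Yes, as a difference in change |
| As above, plus run × time | 6 | 5 | No |

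In both models with pre-dose samples, AP 1000 mg versus AP 2000 mg stays estimable, since both doses are in the same run. On the log scale a proportional change in sensitivity is an additive shift, so it cancels in the pre-to-peak change. A run effect on the size of that change does not cancel.

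**2. What a comparison of hit lists does when the drugs do not differ**

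Input from the document: n = 18 subjects, each with a pre-dose and a peak sample per arm (section 2.3.6). Assumed inputs: true log change 0.20 under both drugs, biological SD of the change 0.25, two-sided p < 0.05, paired t-test, technical CV 15% in run 1 and 15% to 30% in run 2, independent errors between runs.

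SD of the observed change = √(0.25² + 2·CV²); noncentrality = 0.20·√18 / SD.

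- CV 15%: SD = √(0.0625 + 0.045) = 0.328; noncentrality 2.59; power 68%.
- CV 20%: SD = √(0.0625 + 0.08) = 0.377; noncentrality 2.25; power 56%.
- CV 30%: SD = √(0.0625 + 0.18) = 0.492; noncentrality 1.72; power 37%.

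Metformin only = P₁(1 − P₂); AP only = (1 − P₁)P₂; discordance is their sum. Results use unrounded powers.

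| CV run 1 / run 2 | Metformin only | AP only | Discordant |
|---|---|---|---|
| 15% / 15% | 22% | 22% | 43% |
| 15% / 20% | 30% | 18% | 48% |
| 15% / 30% | 43% | 12% | 55% |

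Unequal noise adds up to 12 percentage points of discordance in this range. It also tilts the discordance: single-drug findings that split evenly under equal noise run nearly four to one towards metformin at 30% CV (43% against 12%).

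**3. The alternative analysis under the same null**

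A simulation used 18 subjects, 20,000 features and the same true effect in both drugs (assumed: between-subject SD 1, within-subject SD 0.5, effect 0.6, analytical SD 0.3 in run 1 and 0.3 to 1.0 in run 2, additive run shift 0 to 1).

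- Direct peak-to-peak comparison, equal noise, run shift 0.5 or 1: falsely significant in 68% or 99.8% of features.
- Hit lists: 28% discordant with equal noise, 44% with analytical SD 0.6 in run 2 and 62% with 1.0.
- Paired comparison of within-arm changes: falsely significant in 4.7% to 5.2% of features in every setting.

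**The case against.** The strongest case against has four parts.

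*Separate runs are not stated.* First and second analysis may describe when data were analysed and reported, not when samples were injected. Sorting samples by subject, time point and processing batch (section 2.3.7) would also fit batches that mix arms. Tense does not settle it, since section 3.3 writes the metformin work in the future although section 3.4 says it is published. This stands in part. The published first analysis and a workflow repeated for AP make separate acquisition the likelier reading, but the point must stay conditional.

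*The protocol plans no direct intensity comparison between drugs.* This stands. A reader might infer that drug and run cannot be separated at all, or that the planned batch correction would erase the drug difference. The documents support neither. Each arm has its own pre-dose samples, so additive shifts cancel, and nothing says that batch correction is applied across the two sets.

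*Most of the discordance is there without any run difference.* This also stands: 43% with equal noise in the illustration. It argues for changing the comparison first and the acquisition second, because co-injection alone would leave a comparison of significance lists at n = 18.

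*Batch make-up is laboratory detail for the full protocol or the supplementary workflow, which are not shown.* This is fair for run order and quality-control detail, and their absence is not the point here. The article itself fixes the sequence and the comparison of per-arm pathway results across it.

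**Conclusion.** The concern holds in a limited, conditional form. If metformin and AP were acquired in separate runs, run differences in noise, detection or response size are aliased with metformin versus AP, and comparing per-arm lists of significant features or pathways can show a drug difference where there is none. The pre-to-peak contrast within each arm is not affected. A reader might extend the problem to all three arms, but AP 1000 mg versus AP 2000 mg is sound on this point if both doses share a run.

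The size is illustrative: 55% discordance against 43%, tilted 43% to 12%, under assumed effect, SD and CVs. The calculation is per feature and does not carry over directly to pathways. This is worth correcting before the cross-drug comparison is made, even in an exploratory study, because that comparison is a stated objective.

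**What to change.** In section 3.3, for the cross-drug objective only:

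1. Replace the comparison of significance lists by a paired within-subject comparison of within-run post/pre log ratios, metformin against each AP dose, limited to features detected in both runs, with no batch correction across the two sets. This costs analysis work and leaves fewer comparable features. It removes additive shifts on the log scale, but not a run effect on the size of the response.
2. Where stored aliquots remain (section 2.3.7 provides three per plasma sample), preferably acquire the AP samples together with re-injected metformin pre-dose and peak samples in one randomised run with a common pooled quality control. The extra load is 18 × 2 = 36 metformin samples, or 36 × 2 = 72 injections over the two ionisation modes, with no new subjects or procedures. This also deals with run effects on response size and detection. The analysis in item 1 should still be used.
3. State which arms each acquisition batch holds. If the sets cannot be linked, report metformin-versus-AP pathway differences as descriptive only.

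One limit remains whichever route is taken. The Abstract selects the peak sample by individual Cmax for metformin and by median Cmax for AP, so the sampling rule also differs by drug and should be named when the comparison is interpreted.

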### 2.2. Ethics Committee and Clinical Trial Registry

This study was reviewed and approved by the Medical Research Ethics Committee (MREC), Universiti Malaya Medical Centre. The ethics committee is recognised by the Forum for Ethical Review Committees in the Asian & Western Pacific Region [34]. The study approval letter (Supplementary Figure S1), ethics committee composition and meeting attendance composition were in accordance with Good Clinical Practice. The research protocol version 4.0 dated 17 September 2019 (Supplementary Document S1), patient information sheet (Supplementary Document S2), and informed consent form (Supplementary Document S3) in both the English and Malay languages, trial advertisement, trial insurance, principal investigator’s curriculum vitae and Good Clinical Practice certificate, and case report form were approved by the Medical Research Ethics Committee, University Malaya Medical Centre (MREC ID Number 2018112-6848) on 18 September 2019. Protocol amendments, protocol deviations, and interim study reports were submitted to the ethical committee.

Independent safety data or efficacy data monitoring committee was formed in this crossover trial to determine the continuity of the study as the doses used for the investigational products are marketed products approved by the Ministry of Health Malaysia. However, serious adverse events or protocol deviations will be notified to the ethics committee according to the written procedure.

The study was also registered with the National Medical Research Registry, Ministry of Health Malaysia (registered number NMRR-18-2907-41284) and Clinicaltrials.gov (identifier number NCT04161404) [35]. The study was conducted in accordance with the Malaysian Guidelines for Good Clinical Practice [36] and the Declaration of Helsinki [37].

### 2.3. Conduct of Study

#### 2.3.1. Trial Site

The study was conducted at the Clinical Investigation Centre, University Malaya Medical Centre. The clinical research ward is equipped with ten hospital beds and an emergency trolley. This is a tertiary university hospital that has an emergency department, and the research ward is connected to an intensive care unit if an emergency occurs. The study personnel were trained for the study protocols and the trial’s detailed procedures. The training record was maintained at the site. The principal investigator delegated trial related activities to the study team and recorded the individual personnel’s responsibilities on the job delegation sheet. The trial activities schedule is presented in Supplementary Table S1 for an explanation of the activities to the trial site personnel.

#### 2.3.2. Inclusion and Exclusion Criteria

The subject inclusion criteria comprised male subjects aged 18 to 45 years with a body mass index between 18.5 and 29.5 kg/m^2^, non-smokers who were legible, and willing to provide written informed consent. Subject exclusion criteria included subjects suffering from any chronic illness, history of a pre-existing bleeding disorder, alcohol or drug abuse, kidney or liver dysfunction, suffering any psychiatric disorder, positive HIV, or hepatitis B or C, clinically significant abnormal electrocardiogram or abnormal laboratory screening evaluation, systolic blood pressure of 100–139 mmHg, diastolic blood pressure of 60–89 mmHg, pulse rate of 60–100/min, oral temperature more than 37.5 °C, history of allergy to the investigated product, the existence of any surgical or medical condition under the principal investigator judgement’s that might interfere with the absorption, distribution, metabolism, or excretion of the drug or is likely to compromise the safety of the volunteers and the inability to communicate or cooperate.

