#### 2.3.7. Screening and Data Collection

Subjects will be screened for the eligibility criteria according to the screening case report form after signing the informed consent form. The principal investigator will perform the physical examination, review the demographic data, electrocardiogram, vital signs, biochemistry, haematological, serological, urinalysis test, and perform the interview questionnaire to determine the subject’s eligibility. Eligible subjects will attend the dosing day at the trial site and will be asked to fast for at least ten hours to reduce the variability of drug absorption. Eligible subjects will then be asked to attend a method validation visit to collect additional blood and urine samples.

On the dosing day, the study coordinator will record the subject attendance list, subject enrolment list, subject identification list, and subject randomisation sheet. Subjects will be assigned to the randomisation group by the study coordinator. Pre-dose urine samples and plasma samples will be collected before dosing. After single-dose oral administration, fourteen blood samples will be collected at 0.5, 1, 1.5, 2, 2.5, 3, 3.5, 4, 5, 6, 8, 10, 12, and 24 h post-dose. The actual sampling time will refer to the subject plasma sampling schedule (Supplementary Figure S6) and subject urine sampling schedule. An indwelling intravenous cannula will be used to collect the pre-dose and up to 12 h post-dose blood sample by syringe. The blood samples will then transferred into a pre-labelled potassium ethylenediaminetetraacetic acid (KEDTA) tube. The heparin-lock technique will be performed to prevent clotting of the blood by injecting 1 mL of heparinised saline in the indwelling cannula. Ambulatory blood will be collected at 24 h post-dose. The blood samples will then be centrifuged at 35,000 rpm for 15 min at 20 °C, and the plasma separated into three aliquots in cryotubes and stored at −80 °C in a freezer. The post-dose urine samples will be collected at three periods: period U1 (0–4 h post-dose), U2 (4–8 h post-dose), and U3 (8–12 h post-dose. The urine samples will then be separated into three aliquots in cryotubes and stored at −80 °C in a freezer. The study activities will be recorded on the case report form.

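### The exclusion criteria list normal blood pressure and pulse ranges as reasons for exclusion, so as written almost no healthy volunteer is eligible

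*Protocol article*

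**What the plan says.** Section 2.3.2 of the protocol article has two sentences. The first gives the inclusion criteria: "male subjects aged 18 to 45 years with a body mass index between 18.5 and 29.5 kg/m^2^, non-smokers who were legible", plus willingness to consent. It contains no blood pressure or pulse limit.

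The second opens "Subject exclusion criteria included subjects suffering from any chronic illness" and runs on as one list. Within that list stand "systolic blood pressure of 100–139 mmHg, diastolic blood pressure of 60–89 mmHg, pulse rate of 60–100/min", followed directly by "oral temperature more than 37.5 °C".

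Section 2.1 describes a "randomised-controlled trial in healthy volunteers under the fasting condition". It gives the screening plan as "Approximately 24 to 27 subjects were screened for a list of inclusion and exclusion criteria" "to recruit up to 18 healthy volunteers with the estimation of 30–50% ineligibility".

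Section 2.3.7 has the principal investigator "review the demographic data, electrocardiogram, vital signs, biochemistry, haematological, serological, urinalysis test" to decide eligibility, but states no limits. Section 2.3.2 is therefore the only place in the text shown where vital-sign limits for eligibility appear.

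**The concern.** Every other item in the exclusion list names something that disqualifies a volunteer: an illness, an abnormal test, a raised temperature. The three vital-sign items instead give ranges that most healthy young men fall into, with no word such as *outside*, *below* or *above*. Taken literally, the rule turns away volunteers with ordinary readings and leaves only those whose systolic pressure, diastolic pressure and pulse are all outside the ranges.

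Eligibility determines to whom the safety, pharmacokinetic and metabolomic results apply. If the text were applied as it stands, the target population would be reversed, the screening numbers could not be met, and a single-dose study under fasting would select on abnormal haemodynamics. The article also presents itself as a framework for other early-phase trials, so a reader who copies the criteria copies the inversion.

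**Working it through.** **1. Direction of the text.** The governing phrase is the exclusion phrase. The item before the three ranges (abnormal laboratory screening) and the item after them (temperature above a threshold) both name abnormal findings. The three ranges alone name acceptable-looking values. The sentence is continuous, with no sign of redaction or missing text.

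**2. The plan's own figures.** Expected ineligibility of 30–50% means 50–70% eligible. The screening numbers give 18/24 = 75% and 18/27 = 67% eligible. The two statements differ somewhat, which is a separate matter, but both expect at least half of those screened to qualify.

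**3. Assumptions.** The article gives no vital-sign distributions, so these are assumed: normal distributions with mean (SD) as tabulated, readings rounded to whole units, pulse independent of blood pressure, and *r* the correlation between systolic and diastolic pressure. Results come from 2 million simulated volunteers per row.

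- Literal rule: eligible = P(SBP outside 100–139 and DBP outside 60–89 and pulse outside 60–100)
- Number to screen = 18 / eligible

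| SBP | DBP | Pulse | r | Inside each range (SBP / DBP / pulse) | Eligible, literal | Screen for 18 |
|---|---|---|---|---|---|---|
| 115 (10) | 72 (8) | 72 (9) | 0.6 | 93.3% / 92.7% / 91.7% | 0.18% | 10,045 |
| 120 (12) | 75 (9) | 70 (10) | 0.6 | 90.4% / 90.4% / 85.2% | 0.43% | 4,158 |
| 125 (15) | 78 (11) | 66 (12) | 0.7 | 78.9% / 80.6% / 70.4% | 2.98% | 604 |
| 120 (12) | 75 (9) | 70 (10) | 0 | 90.4% / 90.4% / 85.2% | 0.14% | 13,211 |

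**4. Hand check for 120 (12), 75 (9), 70 (10), without rounding.**

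- SBP outside: 0.048 + 0.057 = 0.105
- DBP outside: 0.048 + 0.060 = 0.108
- Pulse outside: 0.159 + 0.001 = 0.160
- All three independent: 0.105 × 0.108 × 0.160 = 0.0018, or about 0.2%
- SBP and DBP fully dependent: 0.105 × 0.160 = 0.017, or 1.7%; 18 / 0.017 is about 1,060 screened

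Rounding to whole units widens each range by half a unit at each end, which is why the independent case in the table is slightly lower (0.14%).

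**5. A bound that needs no correlation assumption.** Eligibility cannot exceed the smallest of the three outside-range fractions. In the most permissive row that is DBP: 1 − 0.806 = 19.4%, so at least 18 / 0.194 = 93 screened. In the first row it is SBP: 1 − 0.933 = 6.7%, so at least 18 / 0.067, about 270. Both are far from 50–70% eligible and 24 to 27 screened.

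**6. A softer reading.** Suppose exclusion applied only when all three values lie in range together. The share with all three in range is 80.8%, 71.4%, 48.9% and 69.7% by row, so about 49–81% would be excluded, and they would be exactly the volunteers with unremarkable readings. The direction is still wrong.

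**7. The ranges read as acceptable values.** The same shares become the eligible fraction: 18 / 0.808 = 22 up to 18 / 0.489 = 37 screened, on vital signs alone. That is the same order as the 24 to 27 stated, which supports an inversion of direction. It is illustrative and does not establish the intended limits.

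**The case against.** The strongest reply is that this is a slip that nobody acted on. Section 2.1 reports screening in the past tense, and section 3.4 says the metformin analysis has been published, so recruitment was evidently not blocked. The intended meaning is easy to guess from the healthy-volunteer label and from the neighbouring items on abnormal findings. The operative documents, protocol version 4.0 and the case report form (section 2.2), are not shown and may be worded correctly. The same sentence also excludes chronic illness and anything the principal investigator judges unsafe, so even a literal reading would admit almost nobody rather than admit unsafe volunteers. Finally, the screening counts depend on assumed distributions.

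Most of this stands as a limit on practical harm. There is no evidence of wrong enrolment, and the safety and recruitment consequences are conditional on literal use. The screening figure is best given as a wide range. None of it makes the sentence right. This is a criterion stated in the wrong direction, not a detail left to a fuller document, and a reader should not have to guess an eligibility rule. The contradiction with the healthy-volunteer population needs no assumed distribution at all.

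**Conclusion.** The concern holds. Section 2.3.2 states the blood pressure and pulse criteria backwards and contradicts section 2.1 on both the population and the expected ineligibility.

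Under the assumed distributions, each range alone would exclude about 70–93% of healthy young men. The literal rule would leave 0.1% to 3.0% eligible, or roughly 600 to 13,000 screened for 18. Whatever the correlation between the three measures, eligibility stays below 20% in every case tried, against the 50–70% that the article implies. The exact count depends on the assumed means, SDs and correlation; the conclusion does not.

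A drafting error is by far the likeliest explanation. Because it concerns a core eligibility rule and costs almost nothing to correct, it must be fixed.

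**What to change.** Reconcile the sentence in section 2.3.2 with the approved protocol version 4.0 and the screening case report form. Depending on what those documents say, either move the three ranges to the inclusion criteria or word them as exclusion of values outside the ranges. The limits themselves should come from the approved documents; none is proposed here.

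Check the screening form for the same inversion. If it is there, correct the form and the protocol as well, and confirm how the criterion was applied to the volunteers already screened.

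Cost: one sentence in the article and, only if the error is repeated, a matching correction to the protocol and form. Sample size, design and analysis are unaffected.
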